### Patient health questionnaire-9 (PHQ-9)

The PHQ-9 uses 9 items to ascertain how often individuals have demonstrated depressive symptoms in the past two weeks. Each answer option is scored from 0 to 3, so the total range goes from 0 to 27. Scores of 5, 10, 15, and 20 are the cut-off points for absence of depression, mild depression, moderate depression, moderately severe depression and severe depression, respectively. Studies have shown that the PHQ-9 tool has good validity, reliability (α = 0.799), sensitivity (0.72) and specificity (0.76) for screening depression in primary health care units [28].

### Patient health questionnaire-15 (PHQ-15)

The PHQ-15 uses 15 items to ascertain how often participants have been inconvenienced by somatic symptoms in the past four weeks. Each answer option is scored from 0 to 2, with the total thus ranging from 0 to 30. Scores of 5, 10 and 15 are the cut-off points for low, medium or high severity in terms of somatic symptoms, respectively.

### Patient health questionnaire - panic disorder (PHQ-PD)

The PHQ-PD section of the PHQ includes 15 items that make it possible to detect the presence of panic disorder. The first three questions include elements from the Diagnostic and Statistical Manual of Mental Disorders-IV classification system to review the history and frequency of panic attacks (i.e., “In the past 4 weeks, have you had an anxiety attack or sudden feeling of fear or panic?”). The next questions contain information related to the somatic symptoms of panic attacks (i.e., “shortness of breath” or “tingling or numbness in parts of the body”). There are two response categories: “no” (0 points) and “yes” (1 point). The Spanish version of this assessment will be used, which demonstrates appropriate psychometric properties and acceptable sensitivity and specificity levels [29].

Patients are considered to have a positive score in the PD section if all four parts of question 3 (a-d) are answered in the affirmative (4 points), along with [sic] four items from question 4 regarding somatic symptoms (4 additional points). However, since the primary objective of the screening tools is to achieve a high detection rate, we made several modifications to this evaluation algorithm in an attempt to increase the test’s sensitivity in detecting PD. The original assessment algorithm requires affirmative responses for the first four answers to question 3. In contrast, our modified algorithm requires an affirmative response to the first item (3a) and one affirmative response for items 3b, 3c or 3d [29].

### Sheehan disability inventory (SDI)

The original SDI is a 5-item self-reporting tool. In the first 3 items, the patient’s functionality at work or school and their social and family life are evaluated using visual scales, each with 10 points. Scores ≥ 5 on any of the three scales are associated with severe dysfunction. The last two items evaluate the number of lost or unproductive days due to the dysfunction. Santolaya Prego de Oliver et al. [30] found that a 4-item unifactorial model of this scale (SDI-4) had good and acceptable discriminatory and predictive validity respectively, and is an appropriate tool for evaluating disability due to depression in patients who attend Spanish PHC centers.

### WHO QoL BREF quality of life scale

WHOQoL-BREF is a self-report that assesses four areas of quality of life: physical health, psychological health, social relationships and environment. There are also two items that measure general health and quality of life, respectively. The total scale consists of 26 items, and participants respond based on how they felt in the past two weeks. The answers to each question are based on a 5-point Likert scale (1 = “not at all” to 5 = “completely”). The raw scores for each area can fall between 7 and 35 for physical health, 6–30 for psychological health, 3–15 for social relationships, and 8–40 for environment. The higher the score, the better the quality of life. This scale has demonstrated good levels of validity and reliability among populations in both Spain [31] and Latin America [32].

### EuroQol-5 D (EQ-5D)

EuroQoL is a simple tool that measures quality of life in terms of health, and it has two main parts. The first is a descriptive system where the participant indicates how they feel on the day of assessment in terms of their ability to move, their personal care, their daily activities, their pain and symptoms of anxiety or depression. The response for each item is based on three options: 1 (no problems), 2 (moderate problems), 3 (severe problems). The higher the score, the worse the quality of life. The second part is a visual analog scale where patients subjectively evaluate the state of their health on the day of assessment (ranging from 0 = worst state of health, to 100 = best state of health). This scale has proven to be a simple, appropriate and very useful tool for evaluating the quality of life of PHC patients [33].

### Ruminative response scale-brooding (RRS-B)

The original RSS contains 22 items, which patients use to indicate what they typically do when they feel sad or depressed. It uses a Likert scale with 4 response options (1 = never; 4 = always), and has two subscales: Brooding and Reflection. When assessing the convergent validity of the subscales, [34] found that the Brooding subscale has a stronger correlation with depressive symptomatology than Reflection. Only the Brooding subscale is used in this study, which was validated in the Spanish PsicAP project [35]. Consequently, the total score of this subscale ranges from 5 to 20; the higher the score, the higher the patient’s melancholic level.

### Penn state worry questionnaire-abbreviated (PSWQ-A)

The PSWQ is a 16-item questionnaire, and the Spanish version has demonstrated good reliability and validity [36]. It uses a 5-point Likert scale (1=“not at all typical of me” to 5=“very typical of me”), and the scale ranges from 16 to 80 points. Scores ≥ 16, ≥40, and ≥ 60 represent levels of low, moderate, or high concern, respectively. This study uses a shortened, 8-item version that assesses worry as an uncontrollable, generalized and excessive phenomenon, which was validated to be used in Spanish primary care patients [35].

### Inventory of cognitive activity in anxiety disorders-panic brief (IACTA-PB)

IACTA is a tool that evaluates cognitive activity in patients with various types of anxiety disorders including panic attacks (14 items), agoraphobia (14 items) and social phobia (20 items). Participants indicate how often they pay attention to cognitive distortions related to these disorders, scoring from 0 (almost never) to 4 (almost always). The higher the score, the higher the likelihood that the patient suffers from an anxiety disorder. This tool has demonstrated psychometric properties for screening this type of disorder [37]. A shortened, 5-item version will be used in this study to assess the thought errors of PHC patients [13]. The validity of this scale has been proven by the international PsicAP teams, and the intention is to evaluate it with the Dominican population by way of this project [35].

### Metacognitions questionnaire-negative beliefs (MCQ-NB)

Using 30 items, the MCQ-30 measures the differences in an individual’s metacognitive beliefs and their tendencies in regards to judgment and monitoring. Each response option is based on a 4-point Likert scale (from 1 = “do not agree” to 4 = “agree very much”). MCQ-30 scores range from 30 to 120 points. The higher the total score, the higher the pathological metacognitive activity. This scale has proven to be reliable and valid among various populations, including in Spain (38–39). In accordance with the Spanish PsicAP model, we will use the MCQ-NB, which contains only 6 items related to negative metacognitive beliefs about uncontrollability and danger [35].

### Cognitive distortions in emotional disorders questionnaire (CDTE)

The CDTE is a tool that evaluates how often certain cognitive distortions appear. It has 24 items, each with a response option ranging from 0 (almost never) to 4 (almost always), with the total score thus ranging from 0 to 96. The higher the score, the higher the levels of cognitive distortion. This questionnaire contains 4 scales that assess the main cognitive distortions that underly the most prevalent emotional disorders (generalized anxiety disorder, major depressive disorder, panic disorder and somatization disorder). These 24 items were tested in a sample of 1,753 participants. After an exploratory and confirmatory factor analysis, the questionnaire showed the presence of 4 factors, each with 4 items; sustained attentional bias (alpha = 0.96); split attentional bias (alpha = 0.95); magnification interpretive bias (alpha = 0.94); and catastrophizing interpretative bias (alpha = 0.96). High levels of discriminant validity were observed with the 4 emotional disorders (COR curve values; >0.80). These results are currently in the publication phase.

### Cognitive emotion regulation questionnaire-27 (CERQ-27)

The CERQ [40] evaluates nine different cognitive strategies that individuals use to regulate emotions when facing a negative event, which are: We will use the validated Spanish version of the CERQ-27, which contains three items per factor [41]. This allows to study the different strategies individually, and also to evaluate two second-order factors: maladaptive (rumination, catastrophizing, self-blame and other-blame) and adaptive strategies (positive refocusing, acceptance, positive reappraisal, refocus on planning, and putting into perspective).

### Treatment satisfaction survey

At the end of the treatment, all participants will assess their satisfaction with the treatment they received and will have the opportunity to rate it on a scale from 0 (“not at all satisfied”) to 10 (“completely satisfied”).

## Patient recruitment

The study will remain open from the beginning of the assessment until the necessary sample is completed.

The data collection process will be completed once it reaches 300 participants. Sample sizeG*Power3 program were used to determine sample size, which prioritizes statistical power. The effect size measures obtained in the Spanish PsicAP clinical trial were taken into consideration, which were moderate to strong. Based on these analyses, the sample size established for this study was 150 participants per study group (n = 300).

It should be noted that participants will only be included in the study after they have given their informed consent. Patients who do not meet the study inclusion criteria will be referred back to their PHC physician for alternative treatments.

## Randomization

The simple randomization method is used in this study to assign participants to one of the treatment groups (experimental or control). This kind of randomization is done using the Excel computer program in a 1:1 scheme, which makes it possible to obtain two homogeneous groups.

## Data collection

After signing the informed consent, the participants are registered in the PsicAP database using alphanumeric codes to keep their identities anonymous. Participants perform pre- and post-treatment assessments digitally using computerized systems. All pre-treatment assessments are done at the centers along with the co-therapist, using tablets that can connect to the internet. The data that is collected is stored on the Survey Monkey platform (surveymonkey.com). The same battery of tests applied at the beginning of the treatment is administered upon completion. Ideally this last battery is also completed at the center together with the therapist, in the same fashion as during the pre-treatment phase. However, the participant will be given the option to complete it on their mobile device via WhatsApp or email using a link provided by the co-therapist. In this case, the co-therapist has the right to contact the participants via telephone in order to remind them to complete the post-treatment and follow-up evaluations.

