## Data analysis

Intention-to-treat (ITT) analysis will be performed. The ITT analysis will include all randomized patients in the groups to which they were randomly assigned. Analysis will take into account noncompliance, protocol deviations, dropouts, and anything else that happens after randomization. The two randomized groups will be compared in the treatment period; posttreatment; and at 3 and 6 months after treatment finalization. In addition, within-subject comparisons will be analyzed, contrasting pretreatment and posttreatment scores. The within-group and between-group differences will be examined using mixed-effect models, since these are considered more accurate than univariate and multivariate repeated measures of variance. Group differences will be analyzed after controlling for baseline levels, gender, age, and treatment center. Analysis will be carried out using SPSS version 21.0 (IBM Corp).

For primary outcomes, will consider group differences in anxiety (GAD-7), depression (PHQ-9), and somatic symptoms (PHQ-15) comparing baseline and post-treatment scores using a mixed-effect model. For secondary outcomes, will check between-group differences in the level of disability on daily life domains (work, social, and family life) and quality of life domains (physical, psychological, social, and environmental). The effect sizes of the treatment on primary and secondary outcomes (mean scores) will calculate by applying Morris’s d statistic, where the standardized effect of the treatment is defined as the difference between groups in mean PPC values, divided by the common standard deviation. In addition, a per-protocol (PP) analysis for primary and secondary outcomes will performer only in the patients who completed all follow-up measurements.

Finally, will calculate additional analyses: recovery, reliable recovery, and deterioration rates. The recovery index was defined as pre- treatment scores above the threshold on any of the three scales and below the threshold on all scales at either the post-treatment or 6-month follow-up assessment. The reliable recovery rate will calculate using a change score based on the standard deviation (S.D.). Thus, will use a change score of ≥5 for the GAD-7 and ≥6 for the PHQ-9 and the PHQ-15.

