## Limitations

Despite all the strengths and benefits that the PsicAP project can offer to Dominican society, it is also necessary to mention its limitations, which have been recognized since its proposal. One of these is the fact that general PHC practitioners only take 7 to 10 min to examine patients, so they may not be able to use the initial screening test with individuals who come to them that could benefit from PsicAP. This makes it difficult to recruit participants. Likewise, another limitation is that not all patients who come to PHC facilities are aware of the importance of treating EDs and, despite suffering from them, refuse to accept psychological help. PHC facilities in the Dominican Republic tend to be frequented by individuals with a lower socioeconomic status who have not received sufficient information about mental health issues or their manifestations and consequences. Also, due to the fact that the individuals who go to PHC facilities tend to have lower education levels, many do not meet the criteria to be included in the study since one of the prerequisites is being able to read and write.

Another limitation for the study is the fact that the institutions where patients are being recruited were not chosen at random, but rather by convenience (the institutions that were included had agreed to support the project and provide spaces for its development).

One final limitation of the study is the high risk that participants may not attend all seven sessions required for the PsicAP treatment and may choose to leave at some point, which tends to be a typical limitation in longitudinal studies like this one [13]. One other limitation is the use of self-reports.

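### Reminder calls are discretionary and written only for the link route, so nothing requires that patients who leave the sessions be pursued for outcomes

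*Protocol article*

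**What the plan says.** The Data collection section of the protocol article sets out how outcomes are obtained after baseline:

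- Trigger: "The same battery of tests applied at the beginning of the treatment is administered upon completion".
- Preferred route: "Ideally this last battery is also completed at the center together with the therapist".
- Alternative route: "the participant will be given the option to complete it on their mobile device via WhatsApp or email using a link provided by the co-therapist".
- Reminder: "In this case, the co-therapist has the right to contact the participants via telephone in order to remind them" to fill in the post-treatment and follow-up evaluations.

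The article describes no other retention step.

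Three other sections bear on this. Data analysis states: "The ITT analysis will include all randomized patients in the groups to which they were randomly assigned", and adds: "Analysis will take into account noncompliance, protocol deviations, dropouts, and anything else that happens after randomization". Limitations acknowledges "the high risk that participants may not attend all seven sessions required for the PsicAP treatment and may choose to leave at some point". Therapist training says that co-therapists were trained both to carry out the initial and final assessments and to assist the therapists during the PsicAP sessions.

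**The concern.** An ITT comparison is only as good as the outcome data behind it. The patients most likely to lack a post-treatment score are those who stop coming, and the protocol expects such patients. For them the written procedure has three weak points. The battery is tied to completing treatment. The preferred place is a center they no longer attend. The one reminder is a permission attached to the other route.

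The person who decides whether to call also sits in on the PsicAP sessions. That person therefore knows who is in that arm and has weekly contact with one arm only. Controls receive usual care from the primary care physician. Discretionary effort could differ between arms, in a direction that cannot be foretold.

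If collection depends on attendance and arm, the mixed model rests on outcomes being missing at random. That is doubtful where patients leave for reasons linked to how they are doing. The estimate could then lie closer to the effect in those who stayed than to the effect in all who were randomized, yet be reported as ITT. The question here is who is pursued for outcomes, not when the assessments fall.

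**Working it through.** The plan gives no dropout rate, no missing-outcome rate and no effect in patients who leave, so there is no stated figure to reproduce. The check has three parts.

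**1. Which patients does the written procedure oblige staff to pursue?**

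- Completes the sessions and returns to the center: assessed there.
- Takes the link: may be telephoned, at the co-therapist's discretion.
- Leaves the sessions and does not return: may be offered the link, since the offer is general and made by staff. No sentence requires that it be sent, says when, or requires a reminder.

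The third group is left to discretion. It is neither excluded nor secured.

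**2. Does the planned analysis make up for it?**

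The primary comparison is baseline against post-treatment in a mixed model, controlling for baseline. If baseline is a covariate, a patient with no later score contributes no outcome row. If baseline is one of the responses, the patient stays in the model but adds no direct information on the post-treatment difference. Either way the result relies on missing-at-random. The per-protocol analysis is limited to patients with all follow-up measurements, so it also selects on response and cannot serve as a check.

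**3. How large could the effect be? (illustration; every input is assumed)**

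Let p be the share of PsicAP patients unmeasured, a the effect in those measured and u the effect in those unmeasured. Control loss is taken as unrelated to outcome.

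- Effect over all randomized = (1 − p) × a + p × u
- Overstatement = a − that effect = p × (a − u)

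With a = 0.60 SD and u = 0 to 0.2 SD:

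- p = 15%: 0.85 × 0.60 + 0.15 × (0 to 0.2) = 0.51 to 0.54 SD. Overstatement 0.09 to 0.06 SD.
- p = 30%: 0.70 × 0.60 + 0.30 × (0 to 0.2) = 0.42 to 0.48 SD. Overstatement 0.18 to 0.12 SD.

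The range over both is 0.06 to 0.18 SD.

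The sign depends on the assumptions. If patients leave because they have improved, u exceeds a and the formula gives an understatement. If a share q of controls is also unmeasured and would have done worse than the measured controls by c, the bias becomes p × (a − u) − q × c, which is zero when the two terms are equal.

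Loss of precision is the smaller matter. With 150 per group, two-sided alpha 0.05 (assumed) and d = 0.40 (the smallest effect quoted from the Spanish trial, for somatic symptoms), power is about Φ(0.40 × √(n/2) − 1.96). This gives 93.4% with no loss, 82.6% with 30% loss in each group (n = 105) and 76.5% with 40% loss (n = 90). For d = 0.58 and 0.65 it stays at 94% or more even with half the data lost.

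**The case against.** The strongest case on the other side has four parts.

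- **Leavers are not shut out.** A reader might infer that patients who stop attending fall outside the retention effort altogether. The text does not support that. Participants in general are to be given the link option, the co-therapist supplies the link, and no condition of attendance or arm is attached. Staff can send it to someone who left and telephone afterwards. This stands; what is lacking is an obligation.
- **Unequal effort is not stated.** Pre-treatment assessments are done with the co-therapist without restriction by arm, and co-therapists also carry out the final ones. Controls therefore have the same assessment contact. This stands in part: unequal effort is a risk that discretion allows, not something the documents say will happen.
- **ITT is not contradicted.** A reader might infer that it is. But ITT fixes who is analysed and in which group, a mixed model tolerates missing outcomes under missing-at-random, and leaving the sessions is not the same as refusing a questionnaire. This stands.
- **It is detail that an article leaves out.** Numbers of reminders, intervals and scripts usually belong in the full protocol, which may say more. As to that detail, this is fair. But the article does not stay silent: it writes a reminder rule, makes it permissive and attaches it to one route. The point rests on that wording.

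**Conclusion.** The point holds as a weakness in a stated procedure. Followed as written, the collection of post-treatment and follow-up outcomes in patients who leave the sessions depends on the discretion of staff who also assist in one arm's treatment. The protocol expects such patients and promises an ITT analysis of everyone randomized.

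The size and direction of any bias are unknown. The 0.06 to 0.18 SD is an illustration and should not be cited as an estimate of bias in this trial. It assumes 15 to 30% of PsicAP patients unmeasured, a gain of 0 to 0.2 SD in them, 0.60 SD in those measured, and control loss unrelated to outcome. The 0.60 SD has no source as an effect in attenders; the similar values quoted from the Spanish trial (0.65 and 0.58) are intention-to-treat effects. Nor does the calculation show how much bias better reminders would remove, since they will not recover every patient.

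This is a cheap improvement worth making, not a flaw that invalidates the design.

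**What to change.** Replace the reminder sentence in Data collection with a rule along these lines:

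- Every randomized patient in both arms, whatever the number of sessions attended and unless contact is refused, is sent the link at each planned assessment. Completion at the center remains available.
- Non-responders in both arms receive the same fixed number of reminders at the same intervals: automated messages first, then a telephone call from a script.
- Contact attempts and reasons for non-response are logged and reported by arm.
- Patients who decline the full battery are offered the GAD-7, PHQ-9 and PHQ-15 alone, so that the primary outcomes are kept.

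The cost is an amendment to the wording, scheduling of survey messages and some added calls. The survey platform, the link and the staff who telephone are already in place. The downside is a small extra contact burden for patients.
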